### Consent

Each patient who meets the eligibility criteria will receive a full explanation of the trial aims and rationale, as well as the concept of equipoise. To participate, each patient will have to provide written informed consent to participation, treatment, and data processing. Risks and benefits of both trial treatments will be explained, along with potential complications of compression therapy. At this point they will be given the opportunity to enrol, take time to consider, or not enrol with the assurance that non-participation will not adversely impact further treatment, nor will leaving the trial during follow-up. Three copies of the consent form will be signed (one each for the patient, the patient’s hospital notes and the trial database). Consent for data storage will be discussed and permission sought to contact patients in the future to seek further consent for any further use of collected data.

### Data collection

After screening and enrolment, clinical and demographic data will be collected for each participant using a trial case report form (CRF). These data will be entered into the trial database on an on-going basis.

#### Data protection/storage

The trial database will be stored on a password-protected, desktop computer in UHG. A backup copy will be prepared at the end of each data entry session and stored in a locked filing cabinet. The original data entry CRF will be retained with a copy of the consent form in a locked trial filing cabinet within the Vascular Research Unit. All data shall be monitored by approved trial personnel only and processed and stored in the strictest confidence in accordance with Irish and European Union data protection law. All data will be retained in the care of the principal investigator for a period of 5 years from the closure of the trial.

#### Baseline characteristics

After screening, enrolment and provision of informed consent, the principal investigator or trial nurse will collect the following demographic data:AgeSexHeightWeightBody mass index (BMI)DiabetesSmokingAnaemiaABI (or TBI if ulceration prevents cuff application at the ankle)ImmunosuppressionMedications at time of randomisation and treatment

#### Ulcer characteristics

Along with the above baseline characteristics, the following data related to the wound itself will be documented:Ulcer locationUlcer durationUlcer area (in cm^2^)Depth (in terms of tissue layers involved)Condition of wound edgesUnderminingNecrotic tissue typeNecrotic tissue amount (as a percentage of wound area)Exudate typeExudate amountSurrounding skin colourSurrounding tissue oedemaSurrounding tissue indurationGranulation (as a percentage of wound area)Epithelialisation (as a percentage of wound area)Pain (present or not, and relieved by medications or not)

At follow-up visits only:17.Compliance with compression

These data will be recorded by the trial nurse and a BWAT score and VCSS will be calculated.

At each review appointment, the same data will be collected, and progress of the wound assessed using the BWAT. VCSS will also be monitored monthly.

#### Quality of life data

At their initial visit, and when exiting the trial (ulcer healed or completion of 6-month follow-up), participants will complete a CCVUQ questionnaire [29].

### Treatment regimen

Once patients have been assigned a trial number and randomised, their sealed allocation envelope will be retained. Where possible, enrolment, allocation and treatment will occur on the same day to maximise adherence to trial treatments.

The interventions being tested involve the following core steps

#### TIRS

I.Ultrasound guided puncture of the desired vein using a butterfly needleII.Injection of up to 10 ml Sotradecol foam (max 2 ml 1% Sotradecol agitated with 8 ml air to give 10 ml foam) under ultrasound guidanceIII.Massage of the foam as needed into desired vessels

#### AA

I.Ultrasound guided micropuncture of the desired axial veinII.Placement of a 5 French-gauge sheathIII.Passage of the Clarivein™ device to the proximal end of the treatment areaIV.Activation of the device, followed by withdrawal at a rate of 1 mm/s, while simultaneously infusing Sotradecol.

Variations of these treatments are at the discretion of the treating surgeon as long as the above steps are met. After treatment, all patients will be placed in compression bandages. They will then be followed up monthly at the same site with changes of their compression bandages in between by their local public health nurse (PHN) weekly, or more frequently as needed. If at any follow-up visit, their ulcer is seen to have healed, the time at which it healed will be noted in weeks from intervention. At this point, they will have completed their follow-up and will exit the trial. Patients in whom the ulcer has not fully healed at 24 weeks will also exit the trial. In either case subsequent treatment will be at the discretion of the surgical team.

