### Method of blinding

The trial will be assessor blinded. The trial nurse(s) will assess all wounds prior to randomisation and will be blinded to treatment allocation throughout, performing assessments at each follow-up visit. Patients will be instructed not to reveal the nature of their treatment in follow-up. The operation note from the intervention will be filed in the patient notes to allow intentional or emergency access. All members of the trial team involved in data collection and analysis will not be present when the envelope is opened at the time of treatment.

Any treatment decisions required beyond the trial protocol will be made by a member of the surgical team who is already unblinded.

Ultrasound assessment of treated veins will be avoided unless otherwise indicated, to minimise risk of inadvertent unblinding of assessors.

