### Protocol violations

Inability to tolerate AA or TIRS, or compression bandages will constitute a violation of protocol. Failure to attend follow-up on a single occasion will not constitute a protocol violation, and patients will be contacted by phone to arrange further follow-up. All analyses will be performed primarily on an intention-to-treat basis, but a per-protocol analysis will also be performed.

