#### Subsequent follow-up

Patients will attend monthly follow-up, with instructions to the PHN changing their dressings to continue compression until follow-up in all cases. At follow-up appointments, patients will fill a VCSS questionnaire, and the trial nurse will assess their wound and document the BWAT score. Non-healed ulcers will be placed in compression with any other dressings or adjuncts as appropriate and continue follow-up.

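### Time to healing must be noted as a week, but blinded assessment is monthly, so the value is either the visit week (about 2 weeks late on average) or a date from outside the stated blinding

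*Protocol article*

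**What the plan says.** The recording rule stands under Treatment regimen, in the text after the AA steps, and covers both arms: "If at any follow-up visit, their ulcer is seen to have healed, the time at which it healed will be noted in weeks from intervention". The patient then exits. For the rest, "Patients in whom the ulcer has not fully healed at 24 weeks will also exit the trial".

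The same paragraph sets the visit spacing: "They will then be followed up monthly at the same site with changes of their compression bandages in between by their local public health nurse", weekly or more often. Subsequent follow-up gives that community nurse one task, "with instructions to the PHN changing their dressings to continue compression until follow-up in all cases".

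Method of blinding says that the trial nurses "will be blinded to treatment allocation throughout, performing assessments at each follow-up visit". Patients know which procedure they had: under Implementation they consent to the specific procedure after the envelope is opened, and Method of blinding adds that "Patients will be instructed not to reveal the nature of their treatment in follow-up".

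Secondary objective and Secondary outcomes both restrict time to healing to ulcers that heal. Statistical analysis names Student's t-test or the Mann-Whitney U test for continuous variables. Protocol violations allows a missed visit: "Failure to attend follow-up on a single occasion will not constitute a protocol violation", with a phone call to rearrange.

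**The concern.** The rule asks for the time of healing, in weeks. The only blinded observations are about four weeks apart, and each shows only whether the ulcer is open or closed. The protocol does not say which observation supplies the week.

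Two things are at stake. If assessors write down the visit week, reported healing times are too long and fall on a coarse grid, while a t-test or Mann-Whitney test treats them as exact. If assessors back-date, the value rests on someone the blinding arrangements do not cover. If some do one and some the other, values are not comparable between patients.

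This is a data-collection rule that the protocol itself states, so it is not a detail left to an analysis plan.

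**Working it through.** **Plan's own figure.** The protocol gives no figure for the precision of healing time. Its sample size does reproduce, as an equivalence calculation: 2 × 0.8 × 0.2 × (1.645 + 1.645)² / 0.15² = 153.9, so 154 per arm and 308 in total. It uses only the healed proportion, so nothing below changes it.

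**Inputs from the protocol.** Monthly visits, 24 weeks of follow-up, 80% healed (Sample size) and 154 per arm. **Assumptions.** Visits every 4 weeks (six visits, at weeks 4 to 24) and the shape of the healing curve, which the protocol does not give.

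**Lag if the visit week is recorded: exponential curve, by hand.**
- Rate λ = −ln(0.2)/24 = 0.0671 per week.
- True mean among healers = 1/λ − 24 × 0.2/0.8 = 14.91 − 6 = 8.91 weeks.
- Chance of staying open over one 4-week interval: q = 0.2^(1/6) = 0.765.
- Recorded mean = 4 × [1/(1 − q) − 6 × 0.2/0.8] = 4 × (4.25 − 1.5) = 11.00 weeks.
- Overstatement = 2.09 weeks, or 2.09/8.91 = 23%.

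**Other curves, by simulation (healed ulcers only, 4-weekly visits).**

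| Assumed curve | True mean (weeks) | Recorded mean (weeks) | Excess (weeks) | Relative |
|---|---|---|---|---|
| Exponential | 8.92 | 11.01 | 2.09 | +23% |
| Uniform | 12.00 | 14.00 | 2.00 | +17% |
| Weibull, shape 1.5 | 11.55 | 13.53 | 1.98 | +17% |
| Weibull, shape 2 | 13.44 | 15.39 | 1.95 | +15% |

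The lag for one patient runs from 0 to 4 weeks. With calendar-month spacing (4.35 weeks) the average is 2.20 to 2.32 weeks. If 10% of healing visits were missed and the ulcer was next seen a full interval later (assumption), the average is 2.36 to 2.49 weeks and the largest lag is 8. If healing were instead dated at weekly bandage changes, the average lag would be about 0.5 week.

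**Effect on the comparison between arms.** Simulation with 154 per arm, Weibull shape 1.5, and the planned Mann-Whitney test in healed ulcers only:

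| Hazard ratio | Rejection, exact times | Rejection, visit weeks | Mean difference, exact v visit (weeks) |
|---|---|---|---|
| 1.0 | 5.0% | 5.0% | about 0 in both |
| 1.3 | 17.6% | 17.6% | 0.79 v 0.78 |
| 1.5 | 38.0% | 37.2% | 1.26 v 1.24 |

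**What the proposed analysis gives.** In the same setting at hazard ratio 1.5, a complementary log-log model by visit over all ulcers, with unhealed ones right-censored, rejects in about 90% of simulated trials. Check by the log-rank approximation: events = 154 × 0.80 + 154 × (1 − 0.2^1.5) = 123 + 140 = 263; √(263/4) × ln 1.5 = 3.29; 3.29 − 1.96 = 1.33, so power is about 91%. Nearly all of the gain comes from keeping the unhealed ulcers, not from handling the intervals.

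**The case against.** The strongest reply is that the rule asks for when the ulcer healed, not when it was seen healed. Read literally, an ulcer that closed in week 5 is noted as 5. The PHN changes bandages at least weekly, which fits a rule written in weeks, and such a date would be out by only about half a week. The case report form is not shown and may name the source. This stands in part: the protocol does not state that the visit week is recorded, and the 2-week figure applies only if it is. But the PHN is told only to continue compression, is given no healing record to keep, and is not covered by the blinding arrangements. A PHN date would still come from outside the blinded assessment.

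Three stronger readings are tempting, and the protocol does not support them.
- *Healing times will be unblinded recollections.* Nothing says that recall is used, and nothing says that the PHN knows the allocation.
- *A missed visit adds a whole month.* Protocol violations provides for a phone call to arrange further follow-up, so the added delay depends on how soon the visit is rearranged.
- *The treatment comparison is biased.* Both arms share one visit schedule, so the visit-week lag is about equal in each, and the simulated test results barely change. A differential error would need the source of dating to differ by arm, which the protocol does not suggest.

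It is also fair to say that right-censoring unhealed ulcers changes the endpoint's definition and is not a mere change of model.

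**Conclusion.** The concern holds in limited form. The protocol asks for a week of healing that its blinded assessments cannot supply, and it does not name the source. The visit-week reading dates healing about 2 weeks late on average and raises the mean among healers by 15% to 23%. That range assumes 80% healed at 24 weeks, 4-weekly visits and healing curves between exponential and Weibull shape 2. The alternative reading takes the date from outside the stated blinding.

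The harm is to reported absolute healing times and to the clarity of one secondary endpoint. The between-arm comparison is hardly affected if the visit week is used uniformly, and neither the primary outcome nor the sample size is touched. This is a worthwhile improvement, not a threat to the trial's main conclusion.

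**What to change.** In the recording rule under Treatment regimen, replace the noted week of healing with two dates: the last trial visit at which the blinded nurse saw the ulcer unhealed (baseline, if it is healed at the first visit) and the first trial visit at which it was seen healed. State that healing is not back-dated from patient report.

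Analyse time to healing over all randomised ulcers as interval-censored between those dates, for example with a complementary log-log model by visit. Right-censor unhealed ulcers at their last assessment.

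Say openly that this replaces the healed-only definition in Secondary objective and Secondary outcomes.

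**Cost.** No new data are needed, because the wound is already assessed at every review, and dates already held for enrolled patients can be used. The changes are one sentence in the visit rule, a revised endpoint definition in two places and a different model for one secondary endpoint. StatsDirect may not fit that model, so a second package may be needed.

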### Statistical analysis

Statistical analysis will be performed using StatsDirect Statistical Package version 3 (StatsDirect Ltd., Cambridge, UK.). All analyses will be performed on an intention-to-treat basis, but a per-protocol analysis will also be performed. Continuous variables will be presented as mean (± standard deviation) or median (± interquartile range) based on distribution, with 95% confidence intervals. They will be analysed using Student’s *T*-test for parametric and Mann-Whitney *U* test for non-parametric data. Categorical variables will be described in absolute numbers with percentage frequencies. The chi-squared and Fisher’s exact test will be used.

Trial allocation will be concealed during interim statistical analysis unless a significant difference is found at this point which warrants stopping of the trial or the interim analysis indicates the trial could not be completed within a reasonable timeframe.

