### Randomisation

Once enrolled, patients will be stratified by ulcer size (< 5 cm^2^, 5.1 to 10 cm^2^, 10.1 to 25 cm^2^, > 25 cm^2^) and will be randomised to either arm on a 1:1 basis.

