#### Sequence generation

Randomisation will be done using a computer-generated random number sequence, stratified by ulcer size.

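### Randomisation is stratified by ulcer size and baseline scores are collected, but the named tests use neither; adjusting for both would gain precision at almost no cost

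*Protocol article*

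**What the plan says.** Under Randomisation, "Once enrolled, patients will be stratified by ulcer size", in four bands (below 5, 5.1 to 10, 10.1 to 25 and above 25 cm²), and "will be randomised to either arm on a 1:1 basis". Sequence generation adds: "Randomisation will be done using a computer-generated random number sequence, stratified by ulcer size". Allocation concealment has the envelopes numbered within each stratum.

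Baseline values are collected. Ulcer characteristics lists area and the wound items, and states: "These data will be recorded by the trial nurse and a BWAT score and VCSS will be calculated". The CCVUQ is completed "At their initial visit, and when exiting the trial". The secondary outcomes are built on change from these values: absolute and percentage reduction in area, and changes in BWAT, VCSS and CCVUQ.

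The Statistical analysis section names Student's t-test and the Mann-Whitney U "test for non-parametric data". On the description of categorical outcomes it says "Categorical variables will be described in absolute numbers with percentage frequencies", and on testing them, "The chi-squared and Fisher’s exact test will be used". No stratified or baseline-adjusted analysis appears anywhere in the article.

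**The concern.** The only stratification factor in the design does not appear in the analysis. Where that factor predicts the outcome, a stratified estimate removes between-stratum variation that a pooled comparison keeps as noise. The primary conclusion rests on a 90% interval lying inside 15 points, so its width matters.

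The same applies to the scores: a t-test on change gives up precision that a baseline covariate would recover. Absolute area reduction is a sharper case, because the outcome is tied arithmetically to the starting area.

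This is more than detail left to a statistical analysis plan. The article names its tests, and all of them are unadjusted.

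**Working it through.** **Reproducing the plan's sample size.** Inputs from the Sample size section: 80% healing in both arms, 15-point margin, two-sided 90% interval, 90% power. For equivalence with unpooled variance:

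n per arm = 2p(1−p)(z₀.₉₅ + z₀.₉₅)² / 0.15² = 0.32 × (1.645 + 1.645)² / 0.0225 = 153.9, rounded up to 154, or 308 in total.

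This matches exactly, so the design calculation is also unadjusted. The unadjusted half-width is 1.645 × √(0.32/154) = 7.5 points, with power 0.900.

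**Primary outcome, stratified.** Stratum shares and stratum healing rates are not in the article. I assume shares w of 40/25/20/15% from smallest to largest, with overall healing P of about 80%. With 154 per arm:

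- unadjusted half-width = 1.645 × √(2P(1−P)/154)
- stratified half-width = 1.645 × √(2Σw·p(1−p)/154)

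| Assumed size effect | Healing by stratum, % | Σw·p(1−p) | P(1−P) | Half-width unadjusted | Half-width stratified | Power stratified | n per arm for 90% power |
|---|---|---|---|---|---|---|---|
| None | 80/80/80/80 | 0.160 | 0.160 | 7.5 | 7.5 | 0.90 | 154 |
| Mild | 85/82/76/69 | 0.156 | 0.160 | 7.5 | 7.4 | 0.91 | 151 |
| Moderate | 92/82/72/56 | 0.144 | 0.159 | 7.5 | 7.1 | 0.93 | 139 |
| Strong | 97/87/67/40 | 0.120 | 0.160 | 7.5 | 6.5 | 0.97 | 116 |

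The interval narrows by about 1%, 5% and 13% in the last three rows.

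**Dependence on balance within strata.** Simulation, 10,000 runs, n = 308, no true difference, nominal 90% intervals:

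| Size effect | Allocation within strata | Coverage unadjusted | Coverage stratified | Power unadjusted | Power stratified |
|---|---|---|---|---|---|
| Mild | balanced | 0.898 | 0.894 | 0.898 | 0.901 |
| Moderate | balanced | 0.916 | 0.898 | 0.916 | 0.931 |
| Strong | balanced | 0.939 | 0.898 | 0.937 | 0.966 |
| Mild | simple | 0.896 | 0.899 | 0.901 | 0.904 |
| Moderate | simple | 0.897 | 0.901 | 0.900 | 0.931 |
| Strong | simple | 0.903 | 0.900 | 0.905 | 0.968 |

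The unadjusted interval over-covers only in the balanced rows. The power difference appears under both schemes.

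**BWAT, VCSS and CCVUQ.** With equal variances at baseline and exit and correlation r, the variance ratio of ANCOVA to a t-test on change is (1−r²)/(2−2r) = (1+r)/2. For assumed r of 0.3, 0.5 and 0.7 this is 0.65, 0.75 and 0.85, giving standard-error ratios of 0.81, 0.87 and 0.92. At r = 0.5 the standard error is about 13% smaller.

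**Absolute area reduction.** Reduction = baseline area − exit area. For a healed ulcer the exit area is 0, so the reduction is the baseline area. At the planned 80%, that is about 0.8 × 308 = 246 ulcers. Eligible areas run from 1 to 200 cm², and the top stratum is anything above 25 cm², so stratification leaves much of the variation in size untouched. Swapping one healed 1 cm² ulcer for one healed 200 cm² ulcer in an arm of 154 moves that arm's mean by 199/154 = 1.3 cm², with no difference in treatment effect.

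**Stratum boundary.** The first band stops below 5 and the second starts at 5.1, so an ulcer of exactly 5.0 cm² is in neither and has no defined envelope series.

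**The case against.** The strongest reply is that this is small and errs on the safe side. The planned 90% power holds without adjustment, false equivalence is not inflated, and with a mild size effect the gain is negligible. All of that stands.

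A reader might infer more: that the unadjusted interval is wrongly wide and the 5% test is really stricter. With exact balance within strata, the closed-form rejection rate at the margin would be 4.8%, 4.2% and 2.9% for mild, moderate and strong effects. The article does not support stating this as fact. It specifies a stratified sequence but no blocking, and under simple randomisation within strata the unadjusted interval covers close to 90%. Only the loss of precision holds either way.

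A reader might also assume that size was made the stratifier because it predicts healing. The article gives no reason for the choice.

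It is fair, too, that baseline values are partly used. Change scores subtract them, percentage reduction divides by original area, and stratification limits gross imbalance in size. This narrows the point on the secondary outcomes. It does not rescue absolute area reduction, given the open top stratum.

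The 13% figure cannot be carried over to area. It assumes equal variances, whereas most exit areas will be zero; wound scores may also cluster at exit.

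Finally, the section does not say how the 90% interval will be computed, so a separate analysis plan could still stratify it. The tests that are named, however, ignore the strata.

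**Conclusion.** The point holds as an efficiency improvement, not as a flaw that threatens the primary conclusion. Using the randomisation strata would narrow the primary 90% interval from a half-width of 7.5 points to between 7.4 and 6.5, depending on assumed stratum shares and healing rates; with no size effect nothing is gained.

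For BWAT, VCSS and CCVUQ, the gain in standard error is about 8% to 19% for assumed correlations from 0.7 down to 0.3, with equal variances.

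The case is firmest for absolute area reduction. It follows from the article's own planned healing rate and eligible size range that the unadjusted comparison is largely one of starting size. The 5.0 cm² gap is a separate, plain wording error.

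**What to change.** - **Healing:** estimate a Mantel-Haenszel risk difference stratified by the four size bands, and set its 90% interval against the 15-point margin. The chi-squared or Fisher result can stay as a supporting analysis.
- **BWAT, VCSS and CCVUQ:** use ANCOVA with the baseline value and size stratum as covariates.
- **Area reduction:** include baseline area, preferably on the log scale, as a covariate. Do not log-transform the outcome: healed ulcers have exit area 0, for which the log is undefined. Baseline area is at least 1 cm² by eligibility, so its log always exists.
- **Strata:** define the bands without a gap, for example a first band of 5 cm² or less.

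The analysis changes need wording only, since every variable is already on the case report form. They should be written down before outcomes are seen by arm. The stratum change costs slightly more: enrolment is ongoing with envelopes numbered by stratum, so the envelope procedure needs a dated note on where 5.0 cm² ulcers go and how any already enrolled were handled.

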**Discussion:**

This will be the first time that TIRS has been evaluated with a properly powered randomised trial in the setting of venous ulcer management. Streamlining the management of venous ulcers has broad health economic benefits. If it is found that TIRS is superior or non-inferior to AA, then a less expensive, less invasive injection can be offered as an alternative to AA in an attempt to encourage the healing of venous ulcers. If AA is found to be superior to TIRS, then this would suggest that all patients undergoing ablation in the management of venous ulcers should have their superficial reflux fully treated, building on the evidence of the EVRA trial.

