## Aim

The aim of this trial is to answer the following research question.

In adult patients with venous ulcers, are TIRS and AA equivalent in their ability to increase the proportion of ulcers that heal completely within 6 months of treatment?

Null hypothesis: there is a clinically significant difference in ulcer healing.

Alternative hypothesis: there is no clinically significant difference in ulcer healing.

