## Objectives

### Primary objective

The primary objective is to determine if the proportion of ulcers healing within 6 months of treatment with AA of varicose veins by MOCA or TIRS by peri-ulcer foam sclerotherapy is equivalent.

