### Sample size

Power calculation [25] was informed by existing evidence [11–13, 15], predominantly the EVRA trial [15]. EVRA showed a 95% success rate for ulcer healing at 24 weeks. We anticipated a more modest success rate because our exclusion criteria did not limit participants to those with new ulcers. In addition, TIRS has very limited existing evidence with reporting healing ranging from 83 to 100% [21, 23]. An 80% success rate was felt to be reasonable for both treatments in a non-inferiority trial. A cohort of 308 patients (154 per arm) was required to ensure that if the null hypothesis should be rejected, the limits of a two-sided 90% confidence interval would exclude a difference between the groups of more than 15%, with 90% power at 5% significance level.

Given that existing evidence for TIRS consists mainly of small case series with widely varying healing rates, we planned once the first 50 cases exited the trial (either healed or completed 6 months of follow-up) as a pilot to inform a further power calculation for both superiority and non-inferiority outcomes.

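### The analysis section does not carry over the equivalence criterion used to size the trial; the only test it names for proportions tests zero difference and cannot reject the stated null

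*Protocol article*

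**What the plan says.** All references are to the protocol article.

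- **Aim.** The research question is "are TIRS and AA equivalent in their ability to increase the proportion of ulcers that heal completely within 6 months of treatment". The hypotheses are in equivalence form: "Null hypothesis: there is a clinically significant difference in ulcer healing" and "Alternative hypothesis: there is no clinically significant difference in ulcer healing".
- **Primary objective.** It asks whether the healing proportion with AA "or TIRS by peri-ulcer foam sclerotherapy is equivalent".
- **Primary outcome.** A binary outcome for each ulcer, summarised as the proportion healed at the 24-week review.
- **Sample size.** "An 80% success rate was felt to be reasonable for both treatments in a non-inferiority trial". The section then requires 308 patients (154 per arm) so that, on rejection of the null, a two-sided 90% confidence interval excludes a difference of more than 15%, with 90% power at the 5% level. It also plans a further power calculation, after the first 50 cases, for superiority and non-inferiority.
- **Statistical analysis.** Categorical variables are to be given as counts and percentages, followed by "The chi-squared and Fisher’s exact test will be used". The section mentions no margin, no 90% interval and no rule for concluding equivalence. Its only interval is a 95% one, for continuous variables.
- **Labels elsewhere.** The Abstract's aim and the synopsis's primary objective ask whether the proportions differ. The Abstract's discussion looks ahead to a different claim: "If it is found that TIRS is superior or non-inferior to AA".

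**The concern.** The null in the Aim section is rejected by showing that the difference between arms is smaller than the margin. A chi-squared or Fisher test starts from the opposite null, that the difference is zero. A significant result supports a difference of some size, and a non-significant result establishes nothing. Neither outcome bears on the stated null.

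Healing at 24 weeks is the primary outcome and is categorical, so a reader of the analysis section would take these to be its tests. The risk is that a non-significant p-value is reported as showing the treatments to be comparable. That reading becomes easier to reach as the sample shrinks, because a smaller trial has less power to detect a real difference.

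The article intends the result to support offering a cheaper, less invasive procedure in place of AA, so a false finding of comparability would matter. The mixed labels add to this: equivalence, non-inferiority and superiority need different decision rules, and the text does not say which one governs.

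**Working it through.** **Inputs (Sample size section).** Healing p = 0.80 in both arms; margin δ = 0.15; two-sided 90% interval, that is 5% at each limit; power 90%; 154 per arm.

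**1. Reproduce the stated size.** Equivalence of two proportions, true difference zero:

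n per arm = 2p(1−p)(z₁₋α + z₁₋β/₂)² / δ²
= 2 × 0.8 × 0.2 × (1.645 + 1.645)² / 0.15²
= 0.32 × 10.82 / 0.0225 = 153.9, so **154 per arm, 308 in total**.

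This matches exactly. Non-inferiority on the same inputs at one-sided 5%, the level that goes with a 90% interval, gives 0.32 × (1.645 + 1.282)² / 0.0225 = 121.8, so 122 per arm. At one-sided 2.5% it gives 0.32 × (1.960 + 1.282)² / 0.0225 = 149.4, so 150 per arm, but that goes with a 95% interval. The stated number and interval together fit equivalence, although the section calls the trial non-inferiority.

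**2. Compare the two rules at the margin.** Exact binomial enumeration with 154 per arm; uncorrected chi-squared at two-sided 5%; Wald 90% interval for the difference.

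| True healing rates | Chi-squared non-significant | 90% interval wholly within ±15 points |
|---|---|---|
| 80% vs 65% | 15.6% | 5.0% |
| 80% vs 80% | 94.9% | 90.1% |

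The first row is a true difference equal to the margin, where concluding equivalence is an error. The second row confirms that the interval rule has its planned power at the stated size.

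**3. Assumed attrition scenario.** The article gives no attrition rate. If 100 per arm were evaluable, a loss of 54/154 = 35%, the first-row figures would be 33.4% and 5.0%.

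**4. One data set, two answers (hypothetical).** AA 123/154 = 79.9% healed, TIRS 110/154 = 71.4%; AA better by 8.4 points.
- Chi-squared = 2.98, p = 0.084; Fisher p = 0.111. Both are non-significant.
- Standard error = √(0.7987 × 0.2013/154 + 0.7143 × 0.2857/154) = 0.0487. The 90% interval is 8.4 ± 1.645 × 4.87, that is 0.4 to 16.4 points in favour of AA. It crosses 15, so equivalence is not shown.

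**5. The mismatch also runs the other way.** At true rates of 80% and 95%, 4.4% of trials would have a significant chi-squared result while the 90% interval lay inside ±15 points.

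**The case against.** The strongest reply is that the protocol already has a usable criterion. The Sample size section, though awkwardly worded, links rejection of the null to a 90% interval and a 15-point limit. A reader might infer that the trial has no decision criterion at all; that would be wrong. What stands is narrower: the criterion sits in a sizing statement, and the section that prescribes the analysis neither repeats it nor refers to it.

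Second, the sentence on chi-squared and Fisher is generic. It also serves baseline factors, wound features and adverse events, and it is not labelled as the primary analysis. An article may leave the detailed rule to an SAP. This is fair as far as it goes. But the article does name tests for categorical data, gives no other for the primary outcome, and those tests do not fit its own hypotheses. That is a mismatch in what is stated, not missing detail.

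Third, a reader might infer that the investigators will treat p > 0.05 as equivalence. No section says so. The 15.6% is the error rate of that misreading, not of the plan as written. Nor should it be extended to smaller true differences: a 10-point difference lies inside the protocol's own margin, so concluding equivalence there is not an error.

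Fourth, some of the mixed wording reflects a declared intention to look at superiority and non-inferiority after the first 50 cases. That explains the labels but does not supply a rule for each claim.

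**Conclusion.** The point holds in limited form. The hypotheses and the sample size belong to an equivalence design, and the analysis section names only tests of zero difference for the kind of variable the primary outcome is. Because this bears on the primary conclusion, it should be corrected before analysis.

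If a non-significant test were taken as equivalence, the false-equivalence rate at 80% versus 65% would be about three times that of the protocol's own interval rule (15.6% / 5.0%). That figure assumes 154 evaluable ulcers per arm, independent outcomes, the uncorrected chi-squared test and a Wald interval. The 33.4% at 100 per arm rests on attrition that is assumed here.

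**What to change.** 1. In Statistical analysis, state that the primary analysis is the difference in the proportion of ulcers healed at 24 weeks (TIRS minus AA) with a two-sided 90% confidence interval, and that equivalence is concluded only if the whole interval lies within -15 to +15 percentage points.
2. Keep chi-squared and Fisher for other categorical variables, and say that they are not the primary decision rule.
3. Use one pre-stated framework in the Abstract, synopsis, Aim, Primary objective and Sample size sections. Equivalence is the one that matches the hypotheses, the primary objective and the stated number.
4. State in advance the rule for any superiority or non-inferiority claim, for example a two-sided 95% interval excluding zero for superiority.

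The cost is wording in the protocol and in any SAP. No new data are needed. The sample size stays at 154 per arm if equivalence is kept; if the investigators choose another framework, or the planned recalculation changes the assumptions, the number has to be derived again.
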